## FUNDER

This study is funded by an NIHR Programme Grant for Applied Research (PGfAR), ref: RP-PG-1214-20004.

## PROTOCOL INFORMATION

This protocol describes the REDUCE work stream 5 and provides information about procedures for entering participants. The protocol should not be used as a guide for the treatment of other non-study participants; every care was taken in its drafting, but corrections or amendments may be necessary. These will be circulated to investigators in the study, but sites entering participants for the first time are advised to contact [[contact]](mailto:[contact]) at the University of Southampton to confirm they have the most recent version.

## LAY SUMMARY

There is considerable concern about increasing antidepressant use in England. GPs are writing more than 60 million prescriptions a year, to around 1-in-10 adults. Some people need long-term antidepressants to stop them getting depressed, but a third-to-a-half could possibly stop them without relapsing. However, stopping is not always easy. Some patients may experience withdrawal symptoms, while others may be fearful that they will experience them. Withdrawal symptoms can include anxiety and depression, which are usually temporary, but can feel similar to the reasons why patients first started antidepressants. So understandably, some people restart their antidepressant quickly. Others are reluctant to try stopping because they feel well on medication, they are afraid their symptoms may come back, and they feel that there is too much at stake to take the risk of stopping.

Taking antidepressants long-term exposes patients to the risks of side-effects. Common side effects of antidepressants include changes in weight, changes in sleep, and changes in libido or sexual functions. Less commonly, some patients develop bleeding from the stomach or intestine, and the use of antidepressants in people over 65 is associated with an increase in the risks of falls, seizures, and strokes. Some patients also complain that they feel emotionally numb on antidepressants. These are all good reasons for proposing that the drugs should not be continued long-term unless there is a good reason for taking them.

People taking antidepressants have told us their GPs rarely review them and just give repeat prescriptions. Studies show that when GPs do review patients on long-term antidepressants and recommend that they could begin to stop taking them, only 1-in-14 is able to stop. Patients can be fearful and cessation can be tricky, so GPs and Nurse Practitioners (NPs) who prescribe antidepressants need to develop individual cessation strategies for each patient, and be able to offer them sustained support, especially in the first few weeks or months.

The NHS funded six-year **REDUCE (REviewing long term antiDepressant Use by Careful monitoring in Everyday practice)** research programme aims to identify feasible, safe, effective, and cost-effective ways of helping patients taking long-term antidepressants taper off and stop treatment, when appropriate. This Work Stream 5 (WS5) of the REDUCE programme aims to determine the effectiveness of online (Internet) interventions which support practitioners and guide patients on coming off antidepressants, together with psychological practitioner telephone calls to support the patients. This work stream draws on a previous systematic review and qualitative synthesis of the existing literature on antidepressant cessation carried out in work stream 1; analyses of qualitative interviews and focus groups carried out with patients and practitioners respectively on the difficulties of antidepressant cessation in work stream 2; the development of the intervention using 'think-aloud' interviews with patients and practitioners in work stream 3; a feasibility randomised trial in work stream 4; the lived experience of our patient and public involvement (PPI) advisors; and our team's research and development expertise.

WS5 is a fully powered randomised controlled trial (RCT), which aims to assess the effectiveness of the Internet and telephone interventions. It will take 36 months to complete, starting in October 2019. We will recruit 402 patients (201 randomly allocated to the intervention arm and 201 controls), from 134 general practices over 15-18 months,

and follow them up for 12 months. We will assess the effectiveness of the interventions in terms of reductions in antidepressant use in the absence of worsening of depression, and assess patients' and practitioners' use of the interventions (automatically recorded by the Southampton 'LifeGuide' software used for the Internet guidance).

A qualitative process evaluation will be conducted through open-ended interviews with 15-20 patients and 15-20 practitioners in each arm. We will explore why the interventions were effective or not, depending on the results. We will also look at the use of the telephone support provided by psychological practitioners (PWPs), and any technical support needed for patients to be able to use the internet intervention. The interviews will be recorded and typed out (transcribed) for 'thematic analysis', which is line by line examination of the interview transcripts to identify themes among the reactions of the patients and practitioner involved in the trial.

## BACKGROUND INCLUDING OVERVIEW OF THE REDUCE PROGRAMME

Antidepressant prescriptions have risen steadily year on year since 1990, because GPs have been prescribing longer and longer courses (Moore et al, 2009; [name] et al, 2015a), and the average length of treatment is now more than two years. Some people need long-term antidepressants to prevent relapse, but surveys suggest 30-50% have no evidence-based indication for long-term use (Cruikshank 2008). However stopping is not easy, due to withdrawal symptoms including anxiety and mood changes which feel similar to the reason why treatment was started in the first place (Fava, 2015). Patients on long-term treatment are often given repeat prescriptions and are reviewed only infrequently (Middleton, 2011; Sinclair, 2014).

Taking antidepressants long-term exposes patients to the risks of side-effects. Common side effects of antidepressants include changes in weight, changes in sleep, and changes in libido or sexual functions (Ferguson, 2001). Less commonly, some patients develop bleeding from the stomach or intestine, and the use of antidepressants in people over 65 is associated with an increase in the risks of falls, seizures, strokes (Coupland, 2011). Around 1 in 2 patients on antidepressants feel emotional blunting or numbness (Goodwin 2017). So the drugs should not be continued long-term unless there is a good reason for taking them.

Antidepressants constitute a substantial proportion of the NHS drug budget: 2.5% in 2010 (Ilyas & Moncrieff, 2012) and the costs of unnecessary treatment include appointments for medical or nursing reviews. The cost of GP consultations for depression exceeded £30m in 2008 (Independent Research Service of the House of Commons Library), in addition to the cost of the 53 million antidepressant prescriptions per year, of around £300m, so substantial savings could be made if significant numbers of long-term users were to discontinue.

Many patients are dissatisfied with this situation, and would like help to stop long-term treatment. However, GPs often lack experience in reducing antidepressant medication flexibly, and GP advice to taper and stop treatment is not often successful. Prompting GPs to review patients eligible for stopping treatment was tested in a trial in the Netherlands and found to be ineffective, with only 6% of patients discontinuing in the intervention group, and 8% in the control group (Eveleigh 2014; Eveleigh 2015). Similarly, an uncontrolled trial of pharmacist-prompted GP review of long-term users in Scotland resulted in only 7% stopping (Johnston 2012). Therefore it appears that without a specific intervention addressing issues with patient and practitioner behaviours, many patients will continue antidepressants unnecessarily. Practitioners need guidance to provide support for tapering and stopping treatment, and patients need 24 hour support.

## REDUCE PROGRAMME AIM

To identify feasible, safe, effective, and cost-effective ways of helping patients taking long-term antidepressants taper and stop treatment when appropriate.

## REDUCE PROGRAMME OBJECTIVES

1. Conduct a systematic review of interventions used to help patients successfully stop antidepressant treatment.
2. Identify factors promoting or inhibiting treatment cessation, through interviews with patients, and focus groups with practitioners.

3. Develop an internet-supported CBT-based intervention to support treatment tapering and cessation, through co-design and co-production with practitioners and patients.
4. Determine the effectiveness of the intervention through a randomised controlled trial, and estimate cost-effectiveness from a health/social service perspective.
5. Build a translational framework addressing how the intervention should be delivered, including overcoming practitioner and patient related barriers, to facilitate implementation.

## REDUCE WORK STREAMS

### WS1. Systematic review of interventions facilitating antidepressant cessation (October 2016 to September 2017).

The existing literature was searched to inform the planning of our intervention. Papers were identified through comprehensive searches (including Medline/Embase/WHO clinical trials registry/ CINAHL/ PsycINFO/OpenGrey). A thematic synthesis of previous qualitative research was performed, and a narrative review of quantitative studies plus meta-analysis of two pairs of studies: a pair on using cognitive behaviour therapy (CBT) to help with stopping antidepressants, and a pair on using mindfulness based cognitive therapy (MBCT).

Qualitative synthesis of barriers and facilitators (from 21 studies) identified nine important factors: psychological/physical capabilities; perceptions of antidepressants/depression; fear factor; motivators/goals; the doctor as a navigator to discontinuation; information to support decision-making; significant others; support from other professionals. A systematic review of managing discontinuation (15 studies, 12 with analysable results, with meta-analysis possible for 2 pairs of RCTs) showed no difference in cessation rates between CBT + taper (95%) and clinical management + taper (91%), but a lower risk of relapse with CBT. No difference was found in relapse rates between MBCT + taper (achieving cessation in >70%), and maintenance antidepressants.

### WS2. Qualitative interviews with patients and practitioners (October 2016 to September 2017).

Planning the intervention was also informed by 19 individual qualitative patient interviews, and focus groups with 24 GPs, 7 practice nurses, and 6 psychological practitioners (PPs), in the Wessex region. Thematic analysis was used, checking agreement between analysts, and discussing emerging themes with the whole team.

The following themes emerged: patient themes: beliefs about medication, fear of relapse and withdrawal symptoms, patient-practitioner interactions (uncertainty about whether to ask to come off), influence of family and friends; practitioner themes: supporting patients rather than making decisions for them, assessing risk and managing expectations, organisational factors, beliefs, need for psychological tools in the Internet intervention.

### WS3. Co-production of internet-supported practitioner and patient interventions (October 2017 to September 2018).

The interventions were developed based on the literature reviews in WS1 and qualitative interviews with patients and practitioners in WS2, plus theories of behaviour change (Michie) and normalisation process theory (May). Prototype web-based interventions for patients and practitioners were created in LifeGuide, and we used qualitative 'think-aloud' interviews with 15 patient and 19 practitioner participants, to explore whether they were acceptable, interesting, persuasive, and feasible. Thematic analysis of the think aloud interviews was used to identify improvements in the interventions, iteratively, between rounds of interviews. The feedback from users provided information about the positive aspects of the interventions and highlighted areas where improvements could be made. Further iterations of the interventions were then made at stages during WS3 and recruitment for interviews ceased when the feedback was no longer resulting in the need for further changes to the interventions.

The patient intervention includes on-line advice delivered using University of Southampton LifeGuide software on: why try to reduce treatment, dealing with withdrawal symptoms, when to seek help, alternatives to drug treatment, and guided self-help tools based on CBT, MBCT, and acceptance and commitment therapy (ACT).

A separate web-based LifeGuide intervention for the prescribing GPs and nurses includes information and advice on which patients can safely try tapering off treatment, broaching the subject, tapering regimes (including individual antidepressant drug tapering schedules), and schedules for follow-up patient reviews. Telephone support is also provided by a psychological practitioner (PP) for an average of one hour per patient over three calls.

As a result of the think-aloud interviews, two interventions were developed that were informed by the specific needs and preferences of their intended users. Following the completion of interviews, the interventions went through a rigorous testing phase to ensure that all the digital elements worked as intended. The intervention was then ready for use in the feasibility study.

#### WS4. Feasibility RCT, to assess acceptability, recruitment, and outcome measures (October 2018 to October 2019).

WS4 is a pilot feasibility randomised controlled trial (RCT), to assess the acceptability of the Internet and telephone interventions, the recruitment of practitioners and patients, and the acceptability of the planned outcome measures. It will take 13 months to complete, by the end of October 2019, having started in October 2018.

We recruited 52 patients (27 patients randomly allocated to the intervention arm and 25 controls), from 14 general practices over 6 months, and are currently following them up for 6 months. We are assessing ease of practice and patient recruitment; loss of patients to follow-up; the ease of use and acceptability of our outcome questionnaires; and participants' use of the interventions (recorded by 'LifeGuide' software automatically).

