### **2.2 Trial power and sample size**

To have 90% power, with a one-sided alpha of 2.5%, to establish non-inferiority in terms of depressive symptoms within two points (estimated to be the minimal clinically important difference) on the PHQ-9 at 6 months (standard deviation 5.4), we need 155 patients followed up in each arm. Assuming a variable cluster size of between 1 and 7 per practice (mean 3) and an intra-cluster correlation coefficient of 0.012 (from the Health Technology Assessment THREAD trial of treating mild-to-moderate depression in primary care), gives a 1.033 cluster design effect (based on a coefficient of variation of  $1.5/3 = 0.5$ , using the formula of Eldridge). Anticipating 20% do not comply with the intervention and/or are lost to follow-up, we need to randomise  $(155 \times 2 \times 1.036) / 0.8 = 402$  patients (201 per arm) from 134 practices (67 per arm).

Following discussion with the study steering committees and the funder, the sample size was amended to 360 participants. This allows for a correlation between baseline and follow-up scores with a deflation factor of  $1 - \rho^2$ . At the time of review we observed a correlation of 0.47 but were unsure whether this would persist to the end of follow up for all participants. If we assume the more conservative estimate of correlation of 0.26 (the bottom end of the CI), the target sample size to achieve 90% power would 375. We assume the final figure will be somewhere in between 0.26 and 0.47, and that a sample of around 360 will therefore provide us with the necessary 90% power to test reliably for non-inferiority of the intervention in terms of depressive symptoms.

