### **3 Statistical considerations**

#### **3.1 Definition of analysis populations**

##### **3.1.1 Intention-to-treat analysis population**

This population includes all randomised practices and all patients recruited within them regardless of treatment compliance. This includes the participants recruited during WP4 and treated as an internal pilot. All summaries and analysis will be on the modified ITT population unless otherwise specified, i.e. the population as randomised but without missing data imputed. The ITT analysis will be the primary analysis.

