### **4.4 Primary endpoint**

The primary outcome, that is, the differences at 6 months between intervention and control in depression as measured by the PHQ-9, will be analysed using a linear mixed model, adjusting for duration of depression, past history of depression, age, gender, marital status, no. of dependents, ethnic group, education level, economic position (employment status), and accommodation status, baseline depression score, anxiety score, internet use and clustering, including practice as a random effect. These covariates have been chosen based on their known relationship with the outcome from previous literature.

The model will use all the observed data and makes the assumption that missing PHQ-9 scores are missing completely at random. We will examine the lower limit of the 95% confidence interval to establish non-inferiority.

We will then undertake the same analyses using the per protocol population and the CACE population.

Whilst the ITT analysis will be the primary analysis, we will report the analyses based on all three approaches and interpret the findings cautiously in light of any differences between approaches that may emerge. This analysis will form the core of the publication of the trial results.

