#### **4.6 Additional analyses**

No subgroup analyses are planned. Any post-hoc analyses will be exploratory only. Health economic analyses will be undertaken and a separate Health Economics Analysis Plan will be prepared.

In accordance with the CONSORT recommendations for cluster randomised trials, we will also report the ICC for the primary outcome.

Due to the COVID-19 pandemic and subsequent lockdown period, it is possible that there may be changes to the key outcomes unrelated to randomisation group. We will therefore look at the scores in each arm in the pre-, peri- and post-COVID periods in the whole study population. We will use descriptive statistics and graphical representations to explore any trends and aim to control for any time varying effect on outcomes in a sensitivity analysis

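### The primary model pools the 52 WS4 pilot patients without a WS4/WS5 stage term, which could leave the non-inferiority interval slightly wider than it needs to be

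*Combined protocol and SAP*

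**What the plan says.** The protocol presents WS4 as a feasibility randomised trial in its own right, running from October 2018 and due to end by October 2019: "We recruited 52 patients (27 patients randomly allocated to the intervention arm and 25 controls), from 14 general practices over 6 months". The main trial, WS5, was to start in October 2019.

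Under its sample size heading, the protocol proposes carrying the WS4 data forward because the intervention and procedures were essentially unchanged. It leaves the decision to the Programme Steering Committee, informed by the data monitoring committee and the ACCEPT checklist. SAP 3.1.1 then includes them in the intention-to-treat population: "This includes the participants recruited during WP4 and treated as an internal pilot" (the SAP's WP4 is read here as WS4).

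The primary model in SAP 4.4 lists demographic and clinical covariates, ending with "baseline depression score, anxiety score, internet use and clustering, including practice as a random effect". It contains no term for stage or recruitment period. It also omits the three minimisation factors, although the protocol's Statistical Analysis section says the models control for stratification variables.

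SAP 4.6 recognises that outcomes may move over calendar time: because of the pandemic, "it is possible that there may be changes to the key outcomes unrelated to randomisation group". It plans descriptive summaries by COVID period and aims to allow for time effects in a sensitivity analysis.

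**The concern.** The analysis set combines patients from two randomised stages. If the stages differ in mean PHQ-9, randomisation within each stage keeps that difference roughly balanced between arms, so the treatment estimate is hardly affected. The difference is still real variation between practices. With no stage term, the practice random effect has to absorb it, and the standard error of the arm difference rises.

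This touches the quantity that decides the trial. Non-inferiority rests on one limit of the 95% interval against a 2-point margin, and the target was cut from 402 to 360 on a precision argument. The plan has little slack: 360 matches the original requirement only if the baseline to follow-up correlation is about 0.32, and at 0.26 the plan itself asks for 375. What is at stake is a small, avoidable loss of power.

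**Working it through.** **Inputs.** SAP 2.2: "To have 90% power, with a one-sided alpha of 2.5%, to establish non-inferiority in terms of depressive symptoms within two points"; "on the PHQ-9 at 6 months (standard deviation 5.4), we need 155 patients followed up in each arm"; "an intra-cluster correlation coefficient of 0.012"; mean cluster size 3 with coefficient of variation 0.5; 20% non-compliance or loss; amended total 360; correlation between 0.26 and 0.47. Protocol, WS4 section: 52 patients, 27:25, 14 practices.

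**Reproducing the plan's figures.**
- Per arm: the normal formula gives 154. The noncentral t gives 89.97% power at 154 and 90.15% at 155, so 155 reproduces.
- Design effect: 1 + ((0.5² + 1) × 3 − 1) × 0.012 = 1.033.
- Randomised: 310 × 1.036 / 0.8 = 401.5, so 402. (With 1.033 it would be 400.3, so 401.)
- Deflated: 402 × (1 − 0.26²) = 374.8, so 375; 402 × (1 − 0.47²) = 313.2.
- Correlation implied by 360: √(1 − 360/402) = 0.323.

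**Adding an omitted stage shift.** Let D be the WS4–WS5 difference in mean 6-month PHQ-9 that remains after covariates. D is an assumption, since the documents give no value. Take N = 360, so p = 52/360 = 0.144, and 360 × 0.8 = 288 patients followed up.
- Residual variance: s² = 5.4² × (1 − 0.323²) = 26.11.
- Added between-practice variance: a = p(1 − p)D² = 0.1236 × D². Stage is assumed constant within a practice.
- Implied ICC = (0.012 s² + a)/(s² + a); design effect DE = 1 + 2.75 × ICC.
- SE = √(4(s² + a) × DE / 288); power at zero true difference = Φ(2/SE − 1.96).

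Worked for D = 2: a = 0.494; ICC = (0.313 + 0.494)/26.61 = 0.030; DE = 1.083; SE = √(4 × 26.61 × 1.083 / 288) = 0.633; power = Φ(3.16 − 1.96) = 88.5%.

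| Assumed D | Implied ICC | SE | Rise in SE | 95% half-width | Power |
|---|---|---|---|---|---|
| 0 (or term included) | 0.012 | 0.612 | – | 1.20 | 90.5% |
| 1 | 0.017 | 0.617 | 0.9% | 1.21 | 90.0% |
| 2 | 0.030 | 0.633 | 3.4% | 1.24 | 88.5% |
| 3 | 0.052 | 0.658 | 7.5% | 1.29 | 86.0% |

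**Cross-check by simulation.** A REML random-intercept model was fitted with and without a stage term to 14 WS4 practices (7:7 assumed) plus 102 WS5 practices, 1,500 runs for each D.

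| Assumed D | Mean SE without / with term | Ratio | Power without / with term |
|---|---|---|---|
| 0 | 0.620 / 0.621 | 0.998 | 89.3% / 89.5% |
| 1 | 0.624 / 0.621 | 1.004 | 90.5% / 90.4% |
| 2 | 0.636 / 0.623 | 1.022 | 87.9% / 88.7% |
| 3 | 0.654 / 0.621 | 1.052 | 87.5% / 89.4% |

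The simulated effects are somewhat smaller than the formula's, so the two serve as a range.

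**Sensitivity.** The documents do not say whether the 360 includes the 52. With N = 360 or 412 and correlation from 0.26 to 0.47, the formula gives a rise in SE of 0.7–1.0% at D = 1, 2.9–3.9% at D = 2 and 6.4–8.5% at D = 3.

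**Bias from the 27:25 split.** D × (27/180 − 25/180) = 0.011 × D, which is 0.03 points at D = 3.

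**Precision of a WS4-only arm difference.** After 20% loss, 21.6 and 20 patients remain. SE = 5.4 × √(1/21.6 + 1/20) = 1.68, and the half-width is 1.96 × 1.68 = 3.3 points. Multiplying by √(1 − 0.323²) for the baseline correlation gives 3.1. Clustering is ignored.

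**The case against.** The strongest reply is that the effect rests wholly on an assumed shift. Nothing in the documents suggests a stage difference of 2 or 3 points. Two points is the whole margin, and it would have to survive adjustment for baseline PHQ-9, anxiety and about ten other covariates. The protocol's reason for pooling is that intervention and procedures did not materially change. This stands, and it is why the point is of low priority.

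A second reply is that the plan already deals with the matter. It does so only in part. The checklist and committee review govern whether to pool, not how to model the pooled data. SAP 4.3 adds covariates for clinically important baseline imbalance, which a 27:25 split is unlikely to trigger. The time-effect analysis in SAP 4.6 is unspecified and lies outside the primary model.

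The documents do not describe how WS4 was randomised. That its allocation was separate is a fair inference from its being a randomised trial with its own practices and dates, but it is an inference.

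Four stronger readings may tempt a reader, and the material supports none of them:
- That the interval is invalid or could produce a false claim of non-inferiority. The random effect absorbs the shift, so the interval errs on the wide side.
- That the stage term would remove a COVID effect. WS5 was to begin in October 2019 and recruit over 15–18 months, so it may itself span more than one COVID period. The documents do not date those periods.
- That comparing the arm difference across stages would test whether pooling is sound. The WS4 estimate is too imprecise.
- That the discontinuation model would also gain precision. The linear-model argument does not carry over to logistic regression, where adjusting for a prognostic covariate generally raises the standard error of the log odds ratio.

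**Conclusion.** The omission is real, and its consequence is modest and conservative. Under assumed residual stage shifts of 1, 2 and 3 PHQ-9 points, the standard error is too large by about 0.4–0.9%, 2–3% and 5–7.5%. The cost in power is about 0.5 percentage points or less, 1–2, and 2–4.5. At zero shift the term gains nothing and costs essentially nothing. The risk is a slightly greater chance of an inconclusive trial.

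These figures assume that each practice belongs to one stage, N = 360 including the 52, a correlation of 0.323, 20% loss and the plan's SD and ICC. The alternatives examined change them little. This is an optional improvement in precision and transparency, not a fault that threatens the trial's conclusion.

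**What to change.** In SAP 4.4, before unblinding, add a fixed effect for the stage in which the practice was randomised (WS4 or WS5). In the same edit add practice size, location and deprivation, so that the primary model agrees with the protocol's commitment on stratification variables. SAP 4.5 already gives the discontinuation model the same covariates, so it would inherit these terms; the reason there is consistency, not a smaller standard error.

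Keep the pre-, peri- and post-COVID analysis in SAP 4.6 as a separate item. If arm differences are shown by stage, label them descriptive only. State also whether the target of 360 counts the 52 WS4 patients.

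The stage term costs one degree of freedom and a line of SAP wording, with no new data, because each practice's stage is known. The three dichotomous minimisation factors cost one degree of freedom each.
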